## Abstract

**Background:**

The Diabetes Prevention Program (DPP) is highly effective in promoting weight loss in overweight and obese individuals. However, one-on-one DPP sessions are costly. As a cost-saving alternative, a group version of the DPP, called Group Lifestyle Balance program (GLB), has been developed but has been shown to be less effective. The aim of this two-arm parallel randomized controlled trial is to increase the effectiveness of the GLB by integrating habit formation techniques, namely if-then plans and their mental practice, into the program.

**Methods/Design:**

A total of 154 participants will be randomized to a standard or enriched GLB program. For the enriched GLB program, if-then plans and their mental practice will be integrated into the standard GLB program. Participants will be overweight or obese men and women (BMI of 28 to 45 kg/m^2^, waist circumference ≥ 88 for women, ≥ 102 for men, 18 to 75 years of age) who do less than 200 minutes of self-reported moderate or vigorous exercise per week. Measures will be completed at baseline, 3 months, post-intervention (12 months), and 12 months post-intervention (24 months). The primary outcome measure is weight loss at 3, 12, and 24 months. Secondary outcomes include percent reaching weight loss goal, physical activity at 3, 12, and 24 months, and weight-related risk factors (waist circumference, hemoglobin A1c, systolic/diastolic blood pressure, total cholesterol/HDL ratio). Standardized training of the life-style coaches, use of standardized manuals, and audio taping and reviewing of the sessions will ensure intervention fidelity.

**Discussion:**

The study will provide evidence-based data on the effectiveness of an enhanced GLB intervention in promoting weight loss and in reducing weight-related risk factors for chronic health problems. Ethical clearance has been received from the Research Ethics and Compliance Board of the Faculty of Medicine Research and Graduate Studies Office at McGill University (Montreal, Canada).

**Trial registration:**

ClinicalTrials.gov Identifier: NCT02008435. Registered 6 December 2013.

## Background

Being overweight (i.e., body mass index [BMI] ≥ 25 kg/m^2^) or obese (i.e., BMI ≥ 30 kg/m^2^) is one of the leading preventable causes of death in North America, with approximately 500,000 premature deaths each year in the US [1,2]. Overweight and obesity carry the risk of causing health complications, including type 2 diabetes, cardiovascular disease (e.g., heart attack, stroke), hypertension, dyslipidemia, osteoarthritis, and certain forms of cancer [3,4], making such chronic diseases responsible for approximately 39 million deaths annually world-wide [5].

Current evidence suggests that one of the most effective weight loss approaches is a change in dietary and physical activity behaviors through lifestyle modification programs (e.g., cognitive-behavioral treatment programs) [5-11]. Consequently, several lifestyle modification programs have been developed and implemented to promote healthy dietary changes and to increase physical activity [9-14]. The National Institutes of Health Diabetes Prevention Program (DPP) [10] has been found to be the most effective in producing health behavior changes and positive health outcomes. Findings from a DPP randomized controlled trial indicate that individuals lost on average 7% of their body weight through healthy eating and moderate physical activity (150 minutes/week) and reduced the incidence of diabetes by 58% [10]. It was more efficacious than pharmacotherapy (i.e., 31% reduction in diabetes using metformin) [10].

Sustaining the effects of the DPP lifestyle intervention program, however, has proven to be more challenging. After 2.5 years participants re-gained nearly half of the weight lost and their plasma glucose continuously increased [15]. The effectiveness of the program seems to decrease once the contact frequency with the lifestyle coaches decreases. Researchers suspect that participants may not have the tools at hand to sustain their behavior change for life (which is necessary to avoid regaining weight) without continued assistance and encouragement from a lifestyle coach [16]. Moreover, the DPP is costly because it consists of a large number of one-on-one sessions (16 weekly core sessions plus monthly follow-up sessions) delivered by highly trained professionals (at least master’s level) and strategies for motivating participants (e.g., paying for gym fees, exercise videos, etc.) when they have difficulty reaching their lifestyle goals. In response to these concerns, a modified and shortened version of the DPP has been developed by the same research group that developed the DPP: the Group Lifestyle Balance program (GLB) [17]. The GLB uses the same curriculum, and education and cognitive-behavioral techniques as the original program but has a less intensive delivery protocol (only one year, group-based, fewer sessions). It is therefore more cost effective to deliver [17,18]. A recent meta-analysis of all published GLB studies (*N* = 28) found an average weight loss of 4% body weight at 12 months [19]. While clinically important, this is less than the average weight loss achieved in the original DPP trial (7%) [10]. Given that every kilogram of weight lost was associated with a 16% reduction in risk for diabetes in the DPP trial [20], this difference in effectiveness is important. Further, one might also expect that participants regain weight at perhaps even larger rates than in the original DPP after program completion because the GLB is shorter and less intense. Thus, it is pertinent to increase the short- and long-term effectiveness of the GLB through means that compensate for the efficacy lost due to the group-based intervention delivery, lower contact intensity, and shorter duration.

In summary, the DPP is costly, which limits widespread dissemination. The group-delivered version (i.e., the GLB), on the other hand, is cheaper and can thus be disseminated more widely, but it is less effective. Weight regain occurs after both programs. For these reasons, we propose to enrich the GLB with techniques that will result in lasting behavior change. The techniques we propose to integrate into the GLB will facilitate the formation and maintenance of new habits. Ouellette and Wood [21] define habits as “[behavioral] tendencies to repeat responses given a stable supporting context” (p. 55). According to Ouellette and Wood, these cue-behavior chains have to be practiced in order to become automatic. Automaticity of the adopted behavior is the core aspect of habits [22]. Based on the literature of habit change, we have identified *if-then plans* and their *mental practice* as the two strategies for which strongest empirical evidence exists to suggest that they lead to lasting behavior change, i.e. the formation of habits. We have therefore integrated these habit formation techniques into the GLB. This paper describes the protocol of a randomized controlled trial that compares the enriched version of the GLB with its original version.

### If-then plans and mental practice

Two decades of research have provided strong evidence that if-then planning (implementation intentions) and mental practice are crucial techniques for creating strong and lasting habits [23-27]. If-then plans are concrete action plans that specify, in an if-then format, when, where, and how one will act in order to achieve a specific goal (“*If* situation Y occurs, *then* I will initiate goal-directed behavior X!” [26-29]). Forming if-then plans has been found to be much more effective than relying solely on motivation and willpower, as expressed in mere goal intentions (“I will do X”). In fact, a large meta-analysis reported medium-to-large effects of if-then plans on goal achievement across many behavior domains (94 studies, *d* = .65) [28,29]. In a subsequent meta-analysis reviewing physical activity studies, a medium average effect size difference was found [30]. Most importantly, longitudinal studies show that the formed habits are strong and more durable when using if-then planning [31-36]. In the study with the so far longest follow-up interval (48 months), it was found that adolescents in the if-then planning group showed a 34.5% reduction in smoking uptake [32].

Evidence suggests that if-then planning leads to lasting behavior change because the plans render behavioral responses automatic [37]. Specifically, automaticity is achieved because (1) specifying the exact cues in the ‘if’ component prompts the behavioral response that the person committed him/herself to when forming the if-then plan [37]; and (2) the if-then contingency format establishes a strong mental link of causality between the critical cues (‘if’ component) and the chosen behavioral response (‘then’ component) [38]. By explicitly making the causal connection between the critical cues and the goal-directed response through the if-then format, these plans effectively move people from planning to automatically carrying out the behaviours [38,39]. Once automatic, the behavioral response requires little mental effort, contemplative decision-making, self-regulation capacity, or external reinforcement to be carried out [40]. For instance, Milne et al. [36] found that of the people who made if-then plans about when, where, and how to exercise, 100% exercised at the place that they had specified in their if-then plan, 97% exercised at the time that they had specified, and 88% exercised on the day that they had specified.

Creating new habits for complex behaviors such as healthy eating or exercising requires frequent repetition of the same behavior over an extended period of time for it to become habitual. If-then plans can help people to repeat the same behavior over and over again and thereby form habits faster and more enduringly. Mental practice independently has also been shown to improve goal attainment (e.g., [41]). Mental practice (or mental rehearsal) is defined as ‘the cognitive rehearsal of a task in the absence of overt physical movement’ (p 481 [42]). To be effective, mental practice involves the use of multiple sensory modalities, such as imagining the motor movements, objects, situations, emotions through vision, smell, hearing etc. [43-45]. In our own research, we have shown that including mental practice into if-then planning significantly enhances the effectiveness of the if-then plans [23-25]. Combining if-then planning and mental practice is more effective than either if-then planning or mental practice alone [23]. For instance, average daily fruit consumption over a 7-day period more than doubled from pre- to post-intervention in a sample of undergraduate students (from 1.79 to 3.85 portions of fruit/day) after participants were trained to mentally practice their implementation intentions to eat more fruit. There was no increase in the control group [24].

Because of the strong evidence base for the effectiveness of if-then planning, mental practice, and their combination for goal attainment and habit change, we integrated these habit formation tools into the GLB to foster and accelerate the formation of healthy eating habits and increase regular exercise participation. Below, we describe the protocol of the randomized controlled trial that compares the enriched GLB with the standard GLB. The primary outcome will be the mean difference in percent body weight loss between the enriched and the standard GLB at 3, 12 and 24 months. The study is called the *McGill CHIP Healthy Weight Program*. It is conducted in collaboration with the McGill Comprehensive Health Improvement Program (CHIP), which is a multidisciplinary disease management and prevention program that is the primary site of academic research and teaching activities surrounding exercise and health for the McGill medical community. The specific study aims are:

1) To determine the effectiveness of the enriched GLB on weight loss at 3, 12, and 24 months (primary outcomes) and other weight relevant risk outcomes (secondary outcomes) at 3, 12, and 24 months following implementation compared with the standard GLB.

2) To determine whether habits are formed faster (3 months), are stronger at program completion (12 months), and are maintained for a longer period of time after program completion (24 months) in the enriched versus the standard GLB.

3) To determine at 3, 12, and 24 months following implementation whether the effectiveness of the enriched GLB is mediated by stronger habit formation.

## Methods/Design

### Trial design

The McGill CHIP Healthy Weight Program is a randomized controlled trial (RCT) with a parallel group design. Participants will be randomly assigned (1:1) to either the enriched or the standard GLB. Primary and secondary outcome measures are completed at baseline, after 3 months (completion of the 12 weekly sessions, core program), after completion of the program (12 months), and one year after completion of the program (24 months).

### Participants

Participants will be 154 men and women between the ages of 18 and 75 who are overweight or obese (BMI 28-45 kg/m^2^), exercising less than 200 min/week. The trial commenced with a lower BMI criterion of 27. This was changed 3 months into the trial to 28 in order to target a more clinically relevant population. Exclusion criteria include any limitation that would preclude full participation in the intervention or can have a confounding effect on the primary outcomes, specifically: (1) having been diagnosed with diabetes (hemoglobin A1c ≥7.0%); (2) taking the medication metformin (used for treating pre-diabetes or diabetes); (3) having been pregnant in the past 6 months or planning on becoming pregnant in the next 2 years; (4) currently undergoing treatment for cancer; (5) using medication that affects body weight (e.g., loop diuretics); (6) being unable to participate in regular moderate physical activity; (7) having severe uncontrolled hypertension (>190/100 mm Hg); (8) being unable to communicate in English or French; (9) being diagnosed with bulimia nervosa, currently active major depression, or other severe psychiatric disease (including dementia); (10) suffering from a heart attack, stroke, or heart failure within the past 6 months; (11) experiencing excessive weight loss (more than 10 pounds or 4.54 kilograms) in the past 3 months; (12) currently participating in another weight loss program; (13) having had bariatric surgery in the past 2 years or plans on getting it in the near future; (14) planning on moving away from Montreal within the next year; (15) having another member of one’s household enrolled in the program.

### Participant recruitment

Participants are recruited through: (1) flyers and information pamphlets that will be distributed at various clinics, hospitals, and pharmacies; (2) personal communications with the research team, including the nurses and physicians who refer patients to the CHIP and additional local physicians who are in contact with potential eligible participants; (3) emails to 700 individuals who previously were enrolled in one of CHIP’s programs; (4) emails to the members of the YW-YMHA in which the CHIP is located; (5) electronic newsletters of various universities and institutions around Montreal; and (6) advertisement through social media. Interested individuals will contact the research coordinator through email or the phone number published in the information materials.

### Determining eligibility

A 3-step approach for determining eligibility is used: In the first step, upon expressing interest in participation, potential participants receive an email containing more information about the study and a hyperlink directing them to a secure online screening questionnaire assessing the aforementioned inclusion and exclusion criteria. If respondents are not eligible, the online screening session is immediately terminated. Respondents are thanked for their time and participation and asked if they would like to be contacted by CHIP for other potentially suitable programs. In the second step, individuals who are identified as overweight and sedentary are then invited to have their hemoglobin A1c measured at CHIP and their BMI confirmed by examination. The blood sample drawn will be tested in a laboratory, and results will be available within 24 to 48 hours. If the individuals’ hemoglobin A1c level is below 7%, then they are eligible to participate in the study. In the third step, eligible participants participate in a medical exam and a graded exercise stress test (EST) to ensure that they can safely engage in moderate intensity exercise. At this appointment, baseline study measurements are also taken and participants are randomly assigned to one of the two intervention arms.

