### Outcome measures

Measures assessed in the study are reported in Table 1 and described below. The *primary outcome for Aim 1* will be the mean difference in percent body weight loss between the enriched and the standard GLB at 3, 12, and 24 months. Weight loss was chosen as the primary outcome because it was the most important predictor of diabetes incidence in the large-scale diabetes prevention studies [9-11]. Diabetes incidence was reduced by 16% for every kg of weight loss in the original DPP [20]. Weight is assessed with a digital scale without shoes to the nearest 0.1 kg.

**Table 1 T1:** Measures

**Outcomes**	**Variable**	**Measure/source**
**Primary outcome (Aim 1)**	**Mean difference in % body weight loss**	- Weight In Kg (Digital Scale)
**Secondary outcomes (Aim 1)**	**(1) Goal achievement**	
	a. % reaching weight loss goal	- Weight In Kg (Digital Scale)
	b. % reaching exercise goal	- Sum of min. over 7 days (tracking sheets)

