### Randomization

To randomize participants to the two intervention arms, a randomization sheet generated by a random digit generator is used (http://www.randomizer.org). Throughout the recruitment process, the list of randomized numbers will be assigned to participants by the research coordinator in sequential order from 1 to 154 in the order in which participants completes the baseline CHIP appointment. Once a participant is assigned a condition, the research coordinator enters the date and the participant’s initials next to the condition on the randomization sheet. This information together makes up the participant’s anonymous intervention code. Participants are told that the study evaluates two different approaches to lifestyle changes to see if one is superior to the other. Throughout the recruitment process, groups of approximately 6 to 10 people will be created according to their language (i.e., French or English), location, and time of day preferences. It was inherently not possible to blind the interventionist to interventions. However, the staff assessing the outcome variables (e.g. weight, EST) is blind to which intervention the participants were assigned.

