## Trial status

The RCT began participant recruitment in April 2013 and the first groups started in November 2013. Recruitment is currently (May 2014) ongoing until the required sample size is reached.

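### The relocation exclusion covers one year although a primary outcome is measured at 24 months, and baseline weight is fixed before a wait of unstated length

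*Protocol article*

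**What the plan says.** All references are to the protocol article.

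- **Primary outcome** (Outcome measures): the "mean difference in percent body weight loss between the enriched and the standard GLB at 3, 12, and 24 months".
- **Visit clock** (Trial design): visits are tied to the program, that is "after 3 months (completion of the 12 weekly sessions, core program), after completion of the program (12 months"), and the 24-month visit is one year after completion.
- **Relocation** (Participants, exclusion 14): "planning on moving away from Montreal within the next year".
- **Pregnancy** (Participants, exclusion 3): "planning on becoming pregnant in the next 2 years".
- **Baseline and allocation** (Determining eligibility, third step, with the medical exam and stress test): "At this appointment, baseline study measurements are also taken and participants are randomly assigned to one of the two intervention arms". The Randomization section confirms that the list is used "in the order in which participants completes the baseline CHIP appointment".
- **Group formation** (Randomization): "groups of approximately 6 to 10 people will be created according to their language", and also to location and preferred time of day.
- **Dates** (Trial status): "The RCT began participant recruitment in April 2013 and the first groups started in November 2013". Recruitment was still open in May 2014.

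The article states neither a maximum interval from baseline to session 1 nor the interval that occurred.

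**The concern.** There are two timing mismatches, and both touch the primary outcome.

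First, the relocation screen ends long before the last primary assessment. A volunteer who already plans to leave in the second year passes it. The Intervention section places data collection at the CHIP or on the downtown campus, so such a person is a foreseeable risk for a missing 24-month weight.

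Second, weight change is counted from an appointment that comes before group assembly, while the visits are counted from the program. The two arms receive different material from session 1 (Intervention), so I infer that groups are arm-specific and that each person waits for a suitable group in the arm already assigned. Weight gained or lost meanwhile enters percent weight loss and the 7% goal. Exclusions (11) and (12), on recent weight loss and other weight loss programs, guard against such change only up to entry.

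At stake are the completeness of the 24-month data, the precision of the comparison, and what loss from baseline means. The planned precision leaves little room for avoidable losses.

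**Working it through.** **1. The plan's own figure.** From Sample size: SD 4.3 in each arm, accuracy ±1.5 points, 95% CI.

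n = 2 × (1.96 × 4.3 / 1.5)² = 63.1, rounded up to 64 per group. This agrees with the article.

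Half-width at 64 per group: 1.96 × 4.3 × √(2/64) = 1.49.

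**2. Reserve.** The planned 77 per group equals 64 × 1.2 = 76.8, rounded up. With 20% dropout, 77 × 0.8 = 61.6 remain, and the half-width is 1.96 × 4.3 × √(2/61.6) = 1.52. The 64 are kept only up to a dropout of 1 − 64/77 = 16.9%. Higher dropout rates at 24 months (assumed, for illustration) give:

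- 25%: 57.75 per group, half-width 1.57
- 30%: 53.9 per group, half-width 1.62

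Power is not the problem. For the assumed 3-point difference with SD 4.3 it is still about 92% at 40% dropout.

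**3. Calendar.** Let g be the months from the baseline appointment to session 1. The program then ends at 12 + g and the last visit falls at 24 + g. A one-year screen counted from the appointment leaves (24 + g) − 12 = 12 + g months uncovered. From April to November 2013 is 7 months, the largest g the dates allow for the first groups. The value of 3 is an assumed intermediate case.

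| g | End of core sessions | End of program | Last visit | Uncovered before last visit | Program months uncovered |
|---|---|---|---|---|---|
| 0 | 3 | 12 | 24 | 12 | 0 |
| 3 | 6 | 15 | 27 | 15 | 3 |
| 7 | 10 | 19 | 31 | 19 | 7 |

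Counting from the appointment is generous to the plan, because the exclusion criteria are first asked in the earlier online questionnaire.

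**4. Weight drift during the wait, as illustration only.** Assume that drift is independent of later change and applies to everyone. The document gives no drift SD. Total SD = √(4.3² + drift²), and half-width = 1.96 × SD × √(2/64):

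- drift SD 1: total SD 4.41, half-width 1.53
- drift SD 2: total SD 4.74, half-width 1.64
- drift SD 3: total SD 5.24, half-width 1.82

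**The case against.** The strongest case on the other side has five parts.

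- **The horizons may serve different purposes.** The Participants section excludes both what prevents full participation and what can confound the outcome. A one-year relocation horizon fits a one-year program; a two-year pregnancy horizon fits a weight outcome at two years. This stands as an explanation, so the list does not contradict itself. It does not close the gap before the 24-month visit, and with any wait the one-year screen also ends before the program does.
- **Movers may still be measured.** This is true for some, and the number affected is unknown. The Sample size section already allows for around 20% dropout, but step 2 shows that this allowance leaves no slack.
- **Seven months is not a documented wait.** A reader might infer that participants waited that long. The document does not support this. The April date is the start of recruitment, online screening and the A1c test come before the baseline appointment, the first appointment is undated, and nothing is said about later groups. The figure is a ceiling for the earliest recruits.
- **A gap need not bias the comparison.** A reader might infer that the randomized comparison is biased, or that people who drop out before session 1 are removed from their arms. Neither is stated. Baseline is measured at the same appointment for both arms, and waits of equal length do not bias the difference. Bias would need waiting time or pre-start loss to differ by arm. Arm-specific groups make that possible, but nothing shows that it happened.
- **A maximum interval is an operational detail.** An article commonly leaves this to the full protocol. I accept this, and its absence is not the point. The point is the stated order of baseline, allocation, group formation and visits.

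**Conclusion.** The point holds as a cheap improvement to the design, not as an error or an internal contradiction.

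The firm part is the relocation screen. It leaves at least 12 months before the last primary assessment uncovered, and 12 + g months with a wait of g. This rests only on the stated horizon and visit schedule. How many participants it would lose is unknown.

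The softer part is the early baseline. Any weight change during the wait counts as percent weight loss and towards the 7% goal. The wait is at most seven months for the earliest recruits on the stated dates, and its actual length is unknown. The half-widths of 1.53 to 1.82 depend on assumed drift SDs of 1 to 3 points and are not estimates of harm in this trial.

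The consequence is for precision, completeness at 24 months and the meaning of baseline. It matters because the planned half-width, 1.49 against 1.5, has almost no reserve.

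**What to change.** For participants still to be recruited:

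1. Extend exclusion (14) to cover the period up to the planned 24-month visit. The cost is a short amendment and a few more ineligible volunteers. The screen is applied before allocation, so it affects both arms alike.
2. Where scheduling allows, take the baseline weight, and then randomize, as close as possible to the scheduled session 1. The cost is some added scheduling, and the weight should still be taken by the blinded assessment staff.

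For participants already randomized, keep the allocation and analyse everyone as randomized, including those who never start.

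For all participants, report the interval from baseline to session 1 by arm, so that readers can judge whether the waits were short and similar. This needs only dates.

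I would not require randomization within fixed language, location and time cohorts. With groups of 6 to 10, two groups need about 12 to 20 matched people before anyone is allocated. That could lengthen waits, and in small fixed blocks it could make the last allocations easier to predict.
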